### **2.3.2. SECONDARY OUTCOMES**

Secondary (and Primary) outcomes will be compared between participants who underwent surgery and those who did not, and for those who underwent surgery, between those for whom surgery was indicated by AVS only, 11C-Metomidate PET-CT only, or both tests.

Linear, binary logistic, or ordinal logistic regression models will be used, as appropriate. Models will be adjusted for age and sex, and the baseline measure of the outcome (where appropriate). To assess differences between those who underwent surgery and those who did not, a categorical variable for whether surgery was performed will be included. To assess differences between AVS and 11C-Metomidate PET-CT, a 3-level categorical variable for whether surgery

was guided by AVS only, 11C-Metomidate PET-CT only, or both tests, will be included.

Similar models will be used to investigate other predictors of outcome after surgery, in the subset of participants who underwent surgery. In line with the secondary objectives, there is particular interest in the following predictors:

- BP response to therapy with spironolactone/eplerenone, measured as:
  - achievement of home SBP <135 mmHg (or clinic SBP <140 mmHg) at week 4
  - achievement of home SBP <135 mmHg (or clinic SBP <140 mmHg) at week 4, without an increase in other BP medication (as per PASO criteria)
  - change in SBP (home SBP if available, or clinic SBP) between baseline and week 4
  - change in SBP (home SBP if available, or clinic SBP) between baseline and week 4, correcting for changes in other BP medication
- Age, sex, ethnicity
- Baseline BP
- Number of classes of antihypertensive medication at baseline
- Tumour genotype, individually and grouping KCNJ5 mutations vs all other mutations
- Tumour immunohistochemical classification
- AVS parameters
  - Contralateral suppression (aldosterone/cortisol in the contralateral adrenal vein < 50% of aldosterone/cortisol ratio in IVC)
  - Contralateral suppression (aldosterone/cortisol in the contralateral adrenal vein < 100% of aldosterone/cortisol ratio in IVC)
- PET parameters
  - number of nodules on each side
  - 'Probability of adrenal adenoma' on contralateral side'
  - SUVmax (TOF) for [hottest] tumour/normal on side of tumour
  - SUVmax (TOF) for [hottest] tumour/liver
  - SUVmax ratio (tumour /contralateral adrenal) using SharpIR;
- 24h-urine steroid profile

Univariate, and multivariable models will be fitted to explore these associations.

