|----------------------------------------------------------------------------|------------------------------------------------------------------------------------------------------------------------------------------------------------------------------------------------------------------------------------------------------------------------------------------------------------------------------------------------------------------------------------------------------------------------------------------------------------------------------------------------------------------------------------------------------------------------------------------------|
| Study visits (See also 2.3: Schedule of Assessments and Procedures) | Patients will have 10 scheduled visits during the study. Screening visit and one for each PET CT AVS followed by Baseline visit and again at 2 and 4 weeks following start of aldosterone antagonist therapy either spironolactone/eplerenone. Those continuing on medical treatment alone will have one or two further visits between 9 months and 2 years following MDT decision. Those proceeding to adrenalectomy will have as many as possible of the following visits compatible with the overall study end 4 years after study-start: at 1, 3, 6, 12 and 24 months after adrenalectomy. |
| Treatment at study end                                              | It is expected that post adrenalectomy patients will require either no antihypertensive medications or reduced antihypertensive medication which is tailored to their requirements at various points post operatively. For patients who do not proceed to surgery, it is expected that they will continue medical treatment with spironolactone, with change to eplerenone and/or addition of amiloride, if indicated by blood pressure or side effects.                                                                                                                                       |

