## **10.0 Inclusion/Exclusion criteria:**

### **10.1 Inclusion Criteria**

- Male or female: Age >18 yrs.
- Diagnosis of PHA based on current published Endocrine Society consensus guidelines (Funder et al 2016)

- **Patients will be enrolled/consented when they have had each of the following:**

At least one paired measurement of plasma renin and aldosterone, measured off spironolactone/eplerenone and other polluting medications, showing an elevated ARR and.

1. *either* a plasma aldosterone >190 pmol/L after saline infusion
2. *or* 'spontaneous hypokalemia + plasma renin below detection levels + plasma aldosterone > 550 pmol/L)' (as per Endocrine Society guidance, 2016)
3. *or* failure to suppress plasma aldosterone by 30% + persistent PRA suppression after oral administration of captopril (as per Endocrine Society guidance, 2016)

**and** a CT or MRI scan of the adrenals with probable or definite adenoma(s) within the last five years

- Patients with elevated ARR can be put forward for consideration by the MDT as exceptional cases in whom spironolactone/eplerenone is not (fully) withdrawn, and/or saline suppression is not performed, IF:
  1. Plasma Aldosterone > 450 pmol/L **AND** plasma renin <0.5 pmol/ml/hr (<9 mU/L) if measured on treatment with ACEI (Lisinopril ≥20 mg or equivalent) or ARB (Losartan 100 mg or equivalent); OR

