## **21.0 Planned Methods of Analysis**

The planned study analyses will be detailed in the study-specific Statistical Analysis Plan (SAP), which will be finalised in advance of study closure.

The primary outcomes will be analysed in a hierarchical manner:

1. Change in ARR, between baseline and 6 months post-surgery (or equivalent time-point relative to baseline if no surgery), comparing patients who have surgery with patients who do not have surgery.
2. Blood pressure cure rates (home SBP < 135 mmHg on no antihypertensive treatment), comparing patients who have surgery with patients who do not have surgery.
3. ARR in patients who have surgery but have discordant AVS and PET-CT results, comparing patients whose surgery was indicated by high probability PET CT with patients whose surgery was indicated by high-probability AVS.
4. Blood pressure cure-or-control rates (home SBP =20 mm Hg or DBP =10 mm Hg lower than prespironolactone/eplerenone, i.e. baseline) in patients with discordant AVS and PET-CT results, comparing those whose surgery was indicated by high-probability PET CT with patients whose surgery was indicated by high-probability AVS.

5. Blood pressure cure rates (home SBP < 135 mmHg on no antihypertensive treatment) in patients with discordant AVS and PET-CT results, comparing those whose surgery was indicated by high-probability PET CT with patients whose surgery was indicated by high-probability AVS.

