### **1.9. PASO CRITERIA**

The following criteria will be used to define cure of hypertension, from the PASO criteria [Williams TA, et al. Lancet Diabetes Endocrinol. 2017 Sep; 5(9): 689-699], six months post-adrenalectomy.

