#### **Clinical success:**

- Complete clinical success

Complete clinical success will be declared when both (a) and (b) have occurred:

(a) Normalisation of BP, defined as SBP<135 and DBP<85 mmHg on home BP; if home BP not available, then defined as SBP<140 and DBP<90 mmHg on clinic BP

(b) Not taking any antihypertensive medications

- Partial clinical success

Partial clinical success will be declared when the criteria for complete success are not met, and either (a) or (b) has occurred:

(a) reduction in BP, with no increase in antihypertensive medication, i.e. both of (i) and (ii) have occurred:

(i) BP has reduced, or has normalised, since baseline (based on home BP if available, otherwise based on clinic BP); reduction in BP defined as

- (1) a reduction in SBP of  $\geq 20$ mmHg, or
- (2) a reduction in DBP of  $\geq 10$ mmHg, with a change in SBP of  $< 20$ mmHg

(ii) the defined daily dose of antihypertensive medication being used is <150% of baseline

(b) reduction in antihypertensive medication, with no increase in BP, i.e.

(i) BP is unchanged since baseline (based on home BP if available, otherwise based on clinic BP); unchanged BP defined as

- (1) a change in SBP of <20mmHg, and
- (2) a change in DBP of <10mmHg

(ii) the defined daily dose of antihypertensive medication being used is  $\leq 50\%$  of baseline

○ Absent clinical success

An absence of clinical success will be declared when neither partial nor complete clinical success can be declared.

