**Biochemical success:**

○ Complete biochemical success

Complete biochemical success will be declared when both of the following occur:

- Serum potassium  $\geq 3.6$  mmol/l
- Normalisation of ARR ( $ARR_{\text{activity}} < 1000$  pmol/L per nmol/L/hr, if renin activity is recorded, otherwise  $ARR_{\text{mass}} < 91$  mIU/L)

○ Partial biochemical success

Partial biochemical success will be declared when the criteria for complete success are not met, and both of the following occur:

- Serum potassium  $\geq 3.6$  mmol/l
- $\geq 50\%$  reduction in serum aldosterone concentration

○ Absent biochemical success

An absence of biochemical success will be declared when neither partial nor complete clinical success can be declared.

In addition, a modified definition of clinical success (complete, partial, or absent) will be defined as follows:

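### Complete clinical success is a near-foregone contrast between surgical and non-surgical patients, and biochemical success has no rule for follow-up samples taken on an aldosterone antagonist

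*Combined protocol and SAP*

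**What the plan says.** **Clinical success.** SAP 1.9 introduces its success criteria as applying "six months post-adrenalectomy". Complete clinical success needs normal blood pressure and "Not taking any antihypertensive medications". Complete modified clinical success carries the same drug condition.

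**Who is compared.** SAP 2.3.2 says that "Secondary (and Primary) outcomes will be compared between participants who underwent surgery and those who did not". Its models adjust for age, sex and, where appropriate, the baseline value of the outcome. Protocol 21.0 places a similar contrast second in its primary hierarchy: "Blood pressure cure rates (home SBP < 135 mmHg on no antihypertensive treatment), comparing patients who have surgery with patients who do not have surgery".

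**Treatment at follow-up.** Under Treatment at study end, the protocol synopsis says of patients who are not operated on that "it is expected that they will continue medical treatment with spironolactone, with change to eplerenone and/or addition of amiloride". The synopsis entry on the two investigations also has all patients starting or continuing spironolactone or eplerenone. Operated patients are expected to need no antihypertensive drugs or fewer of them; no class is excluded.

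**Biochemical success.** In SAP 1.9, "Complete biochemical success will be declared when both of the following occur": serum potassium of at least 3.6 mmol/l and a normalised aldosterone/renin ratio (ARR). Drug use at the time of the sample is not mentioned. At entry, by contrast, protocol 10.1 asks for a paired renin and aldosterone measurement "measured off spironolactone/eplerenone and other polluting medications, showing an elevated ARR", with exceptions through the multidisciplinary team (MDT).

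**Primary analysis.** SAP 2.3.1 analyses each primary outcome in operated patients only. At least partial and complete biochemical success come first in the hierarchy (SAP 1.8.1). The single sensitivity analysis in SAP 2.3.6 concerns AVS technical failure.

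**The concern.** There are two separate problems.

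First, the surgery versus no surgery contrast on complete clinical success sets a group that may be off all drugs against a group whose expected treatment is itself a disqualifying drug. A very small p-value would be read as a benefit of surgery when most of it follows from the definition. The ARR and potassium contrasts by surgery status have a related weakness: non-surgical samples would mostly be taken on the antagonist and surgical samples mostly off it, and the models do not account for this.

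Second, biochemical success after surgery is the reference standard against which PET-CT and AVS are both judged. If an operation fails, the patient returns to an antagonist or amiloride, and potassium and ARR then meet the cut-offs, the failure is recorded as a cure. That hides a false-positive lateralisation. The two tests are not affected equally, because the planning table expects many more patients positive on PET-CT alone than on AVS alone.

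**Working it through.** The plan states no figure for either problem, so there is none to reproduce. Both calculations below are illustrations.

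**1. Near-zero cell in the surgical contrast**

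Inputs: 70 operated (protocol 23.0) and 149 completers (protocol 16.6), so 149 − 70 = 79 non-surgical patients. This split is an assumption. Success rates in operated patients are also assumed.

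| Operated | Non-surgical | Fisher p |
|---|---|---|
| 14/70 (20%) | 0/79 | 1.2e-5 |
| 24/70 (about 35%) | 0/79 | 1.1e-9 |
| 35/70 (50%) | 0/79 | 8e-15 |
| 35/70 (50%) | 2/79 | 3e-12 |

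The last row allows two non-surgical patients to be off all drugs with normal pressure; the result hardly changes. With a zero cell, the odds ratio is (35 × 79)/(35 × 0), which is infinite. Operated patients have mixed outcomes, so this is quasi-complete separation: the surgery coefficient in a binary logistic model has no finite maximum-likelihood estimate. The three-level ordinal version remains estimable, but its top category has the same dependence on the drug rule.

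**2. Relabelled failures in the accuracy comparison**

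Inputs: the planning table in protocol 33.0, repeated in SAP 1.5. Its cells sum to 100% and return the plan's p: (D+H+I+O+Q)/(D+H+I+G+J+M+O+P+Q) = 20/25 = 80%. The table's normalisation of renin and ARR stands in for biochemical success.

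- Operated: C+D+G+H+I+J+K+L+M+O+P+Q = 56% of recruits.
- Operated and not cured: C+G+I+K+M+P = 1+1+0.5+1+0.25+0.25 = 4%.
- PET-CT positive alone, including unsuccessful AVS: C+D+G+H = 21%. AVS positive alone: I+J = 4%.

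The SAP 2.3.1 rule calls a test accurate if it was unilateral and the patient was cured, or was not unilateral and the patient was not cured.

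- PET-CT: (D+H+L+O+Q+I)/56 = 49/56 = 87.5%.
- AVS: (J+L+O+Q+C+G)/56 = 35/56 = 62.5%.
- Difference: 14/56 = 25.0 points.

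Now let a fraction f of the non-cured in every cell be scored as cured. PET-CT gains f × (C+G+K+M+P) = 3.5f and loses f × I = 0.5f, a net gain of 3f. AVS gains f × (I+K+M+P) = 2f and loses f × (C+G) = 2f, a net gain of 0. The difference is (14 + 3f)/56.

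| f | Difference |
|---|---|
| 0 | 25.0 points |
| 25% | 14.75/56 = 26.3 |
| 50% | 15.5/56 = 27.7 |
| 100% | 17/56 = 30.4 |

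The shift depends on how common non-cure is. If non-cure were 30% in every operated stratum (an assumption well above the table's 4/56 = 7%), the difference would be 17(1 − 2q)/56 with q = 0.3(1 − f): 12.1 points at f = 0, 16.7 at 25%, 21.3 at 50% and 30.4 at 100%.

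The documents do not say in which direction the antagonist moves the ARR. I assume that it can bring it below the cut-off. Protocol 4.2 is consistent with this: it warns of false-negative AVS on these drugs, and of hypokalaemia when potassium-sparing treatment stops.

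**The case against.** Much can be said for the plan.

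- **The primary analysis is already confined to operated patients.** This stands. The first problem reaches a secondary SAP comparison and the protocol hierarchy only. SAP 1.10.3 and 1.10.4 also say that the SAP replaces the protocol's primary outcomes and that an amendment is planned.
- **Non-surgical patients are only expected to stay on the drug.** This also stands. A reader might infer that they cannot reach complete clinical success. The documents do not require that; the rate is near zero, not zero by logic. Partial clinical success remains reachable on treatment.
- **The clinical definition does count the drug.** Correct: it enters as an antihypertensive and through defined daily dose. Only the biochemical definition is silent on it.
- **Better outcomes for this contrast are already listed.** SAP 1.8.2 includes changes in home blood pressure, quality of life, BNP and cardiac MRI. The repair can rely on them.
- **The biochemical rule has some protection.** Partial success needs a fall in aldosterone of at least 50%, and protocol 4.2 describes renewed aldosterone secretion on these drugs, which works against that route. The complete route has no such guard. Protocol 20.2 gives outcome judgement to an endpoints committee, and 24.3 keeps its outcome assessment separate from the test results. That limits bias in judgement but supplies no rule on drug use.
- **Scoring every on-drug operated patient as a failure would add its own error.** This stands. Some will be biochemically cured and treated for residual hypertension, so such scoring does not belong in the primary analysis.

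A reader might also extend the point to potassium supplements. The documents do not show that these lower the ARR, nor that they are recorded with the antihypertensive classes, so I leave them out.

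**Conclusion.** The point holds in two limited parts.

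1. The comparison of complete clinical success by surgery status is largely settled by expected drug treatment and says little about the benefit of surgery. This rests on the protocol's stated expectation for non-surgical patients. The p-values are illustrations on assumed counts. The ARR and potassium contrasts are confounded with drug use in the same way.
2. Biochemical success lacks a rule for samples taken on an aldosterone antagonist or amiloride, and this does reach the first primary outcomes. On the plan's own table the error favours PET-CT by 1.3 points at f = 25%, 2.7 at 50% and at most 5.4 at 100%. It would be larger if non-cure were commoner than planned.

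A reader might infer that the headline accuracy result is seriously compromised, or that about half of all failures would be hidden. The documents do not support either: they give no frequency for return to these drugs, and the shift on the planning table is modest. The gap calls for a stated rule and a sensitivity analysis, not a new primary definition.

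**What to change.** - **SAP 2.3.2 and the planned protocol amendment:** confine complete and complete modified clinical success to operated patients, drop them from surgery versus no surgery testing, and delete step 2 of the protocol 21.0 hierarchy. For that contrast rely on the home blood pressure, quality of life, BNP and cardiac MRI changes already listed. Label the ARR and potassium contrasts as on-treatment and descriptive.
- **SAP 1.9:** keep the biochemical definition for the primary analysis.
- **SAP 2.3.6:** add a sensitivity analysis in which operated patients recorded as taking an aldosterone antagonist or amiloride at the 6-month sample are scored as not biochemically cured, or by the nearest available post-operative sample off these drugs. Report how many are affected by test-result group (PET-CT only, AVS only, both).

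Cost: wording and a little more analysis. SAP 2.2.11 already summarises drug classes at 6 months; check that the coding identifies both aldosterone antagonists and amiloride. The sensitivity scoring may count some true cures as failures, which is why it stays secondary. Nothing changes in patient care.

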#### **1.2.2. SECONDARY OBJECTIVES**

The secondary objectives as listed in the protocol are:

- To investigate whether outcomes differ between those patients who progress to surgery on the basis of PET-CT and/or AVS results, and those patients who do not.

- To investigate whether measurements during 11C-metomidate PET-CT or AVS improve prediction of outcome after surgery.
- To investigate whether blood pressure response to therapy with spironolactone/eplerenone predicts outcome after surgery.
- To investigate whether demographic, genotypic, and pathological data, improve prediction of outcome after surgery.

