### 2.2.2. AVS RESULTS

For the FAS, whether ACTH was administered will be summarised, as will reasons for not administering ACTH. Serum ACTH will be summarised as a whole and in relation to whether ACTH was administered.

For the FAS, the following AVS measures will be summarised as a whole, and in relation to whether the results indicated bilateral adrenal hyperplasia (BAH), unilateral aldosterone-producing adenoma (APA) (left), unilateral APA (right), or were inconclusive:

- Right Adrenal Vein
  - a. Cortisol (maximum value recorded per patient)
  - b. Aldosterone (value corresponding to maximum cortisol)
  - c. Aldosterone/Cortisol Ratio (b/a)
- Left Adrenal Vein
  - a. Cortisol (maximum value recorded per patient)
  - b. Aldosterone (value corresponding to maximum cortisol)
  - c. Aldosterone/Cortisol Ratio (b/a)
- Lateralisation Index (ratio of higher to lower A/C ratio)
- Low IVC
  - a. Cortisol (mean value recorded per patient)
  - b. Aldosterone (mean value recorded per patient)
  - c. Aldosterone/Cortisol Ratio (maximum value recorded per patient)
- Selectivity Index (Right) – ratio of A/C ratios between right adrenal vein and low IVC
- Selectivity Index (Left) – ratio of A/C ratios between left adrenal vein and low IVC

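### SAP 2.3.2 names AVS predictors of surgical outcome only as two cuts of one ratio; a continuous AVS form should be named alongside them

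*Combined protocol and SAP*

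**What the plan says.** SAP 1.2.2 sets the objective for both tests: "To investigate whether measurements during 11C-metomidate PET-CT or AVS improve prediction of outcome after surgery". SAP 2.3.2 gives the method: "Similar models will be used to investigate other predictors of outcome after surgery, in the subset of participants who underwent surgery". It introduces the list with "In line with the secondary objectives, there is particular interest in the following predictors".

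The named AVS predictors are "Contralateral suppression (aldosterone/cortisol in the contralateral adrenal vein < 50% of aldosterone/cortisol ratio in IVC" and "Contralateral suppression (aldosterone/cortisol in the contralateral adrenal vein < 100% of aldosterone/cortisol ratio in IVC". These are two dichotomies of a single quantity.

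There are five PET-CT predictors: a nodule count per side, a contralateral adenoma probability, and three SUVmax ratios for which no cut is given. The ratios are "SUVmax (TOF) for [hottest] tumour/normal on side of tumour", tumour over liver, and "SUVmax ratio (tumour /contralateral adrenal) using SharpIR".

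SAP 2.2.2 derives more from AVS than 2.3.2 uses. It has the A/C ratio in each adrenal vein and in the low IVC, each vein's ratio relative to the IVC (labelled a selectivity index), and a "Lateralisation Index (ratio of higher to lower A/C ratio". There they are for descriptive summary.

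**The concern.** A side-to-side ratio is named as a predictor for PET-CT, but no side-to-side ratio is named for AVS. The one AVS quantity that is named appears only after it has been cut. Cutting a continuous measure usually discards information, and the operated subset is small.

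The SAP does not follow this practice throughout the same list. Response to spironolactone/eplerenone is given both as reaching a threshold and as the change in SBP. AVS has thresholds only, and no reason is stated.

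What is at stake is how the secondary results are read. If the PET-CT ratios show an association and the AVS cuts do not, the reader cannot tell whether AVS carries less prognostic information or was coded more coarsely. A continuous AVS term added after the results are seen would look post hoc.

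**Working it through.** The documents give no power, sample size or alpha for the prediction models, so there is no planned figure to reproduce. The check is a count, followed by an illustration of size.

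**1. Count from SAP 2.3.2**

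| | Named predictors | Uncut ratios | Side-to-side ratio named |
|---|---|---|---|
| AVS | 2, both cuts of one ratio | 0 | no |
| PET-CT | 5 | 3 | yes (tumour/contralateral) |

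**2. Usable AVS results**

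The operated subset is put at 70 (protocol section 23) or 90 (protocol synopsis). In the table in protocol section 33 (repeated in SAP 1.5), the rows where either test is unilateral are:

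- C+D = 11%
- G+H = 10%
- I+J = 4%
- K+L = 30%
- M+O = 0.5%
- P+Q = 0.5%

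The total is 56%. AVS is unsuccessful in C+D, so 11/56 = 20% of operated patients. Assume that these have no usable ratio. Then 70 × 45/56 = 56 remain, and 90 × 45/56 = 72.

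**3. Information kept by a cut**

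For a normal predictor cut at quantile q, with h = Φ⁻¹(q), the share of information kept is φ(h)² / [q(1−q)].

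- 50/50 split: 0.399²/0.25 = 0.64
- 70/30 split: 0.348²/0.21 = 0.58
- 80/20 split: 0.280²/0.16 = 0.49

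Two nested cuts entered together keep about 0.73 to 0.80 for the splits tried, at the price of a second degree of freedom.

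**4. Power by simulation**

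Assumptions: log ratio x ~ N(0,1); logit P(cure) = logit(0.50) + ln(2)·x; likelihood-ratio test, two-sided 5%. The odds ratio and the splits are assumptions. The 50% cure rate is also assumed; it is in line with protocol section 4.3, which expects at least half of operated patients to be cured of hypertension. Ranges cover repeat runs.

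| Usable AVS results | Uncut | Median cut | 70/30 cut | 80/20 cut |
|---|---|---|---|---|
| 70 | 76–80% | 57–58% | 54–56% | 44–49% |
| 56 | 68% | 49% | 46% | 39% |
| 90 | 88% | 69% | 64–65% | 57–58% |

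If 90 are operated and 72 have usable AVS, the first row is the relevant one.

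With 70 results, entering a 50/50 and an 80/20 cut together (2 df) gives about 56%, so having both cuts does not restore the loss.

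With 70 results and 85% cure, power is about 55% uncut against about 30–38% for one cut. This matters for the biochemical outcomes, where the protocol's table implies a high success rate: (D+H+J+L+O+Q)/56 = 52/56 = 93%.

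**5. Reverse case**

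If the true effect is a step at the median (odds ratio 4, 70 results, 50% cure), the cut has about 81–82% power and the continuous form about 63–65%. The ranking therefore depends on the shape of the effect, which the documents do not give.

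**The case against.** A reader might infer that the plan tilts the AVS-versus-PET-CT comparison, or this objective, against AVS. The documents do not support that, for four reasons.

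- The list is one of particular interest and is not stated to be exhaustive. Nothing bars a continuous AVS term.
- No comparison of these predictors between modalities is planned. The AVS-versus-PET-CT comparisons are the paired accuracy analysis (SAP 2.3.1) and the three-level term for which test guided surgery (SAP 2.3.2). Both use the test calls symmetrically and neither uses these measurements.
- SAP 2.3.4 plans ROC and threshold work on continuous measures from both tests. This stands, but it is an additional analysis outside these regression models, and its ROC work rests on an assumption about patients in whom neither test indicated surgery.
- No functional form is given for the PET-CT ratios. That they enter as continuous is the natural reading, but it is an inference.

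A reader might also infer that the cuts are arbitrary or lack support in guidelines. That cannot be checked here. Protocol section 4.2 reports the 100% cut as part of international consensus criteria for lateralisation, so naming it as a predictor is defensible.

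Two technical objections stand and shape the fix. The lateralisation index in 2.2.2 is higher over lower, so it has no side; where AVS was bilateral or pointed to the other gland, it need not describe the operated one. Failed AVS also shrinks the usable set. The power figures rest on an assumed effect size, shape and split.

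What remains is that the only AVS measurements named in advance for these models are dichotomies, while the continuous versions are already derived.

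**Conclusion.** The point holds as a limited improvement to one exploratory secondary objective. The primary accuracy analysis is unaffected.

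Under a log-linear effect with an assumed odds ratio of 2 per SD and 50% cure, naming only cuts costs roughly 20 to 35 percentage points of power. That is from about 76–80% to about 44–58% with 70 usable AVS results, and from about 68% to about 39–49% with 56. The figure of 56 assumes that unsuccessful AVS yields no usable ratio. Under a step effect at the cut the dichotomy does better, which is why both forms should be named rather than one replaced by the other.

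**What to change.** In SAP 2.3.2, under AVS parameters:

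1. Add two continuous predictors: log(contralateral A/C ÷ IVC A/C), and log(A/C on the operated side ÷ A/C on the contralateral side). Define the second by the operated gland, not as higher over lower.
2. Keep the <50% and <100% cuts as named versions alongside.
3. State that the PET-CT ratios enter on the log scale.
4. Fit the AVS models in patients with bilaterally successful AVS, and report that number.

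The cost is a few lines of SAP text. The variables come from values already collected and derived in 2.2.2, so no new data are needed.

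The downside is two more candidate predictors in about 70 to 90 operated patients, fewer where AVS failed. The two new terms share the contralateral A/C value and will be correlated, so the univariate results should be reported as well as any model that contains both.
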